| 
 
To assess evidence of improvement and resolution of ARDS following infusion with agenT-797
 
To assess avoidance of multiorgan dysfunction syndrome
 
 | 
 
Assessment of ventilator-free days
 
Time to extubation
 
Time to intubation in patients with mild ARDS
 
Vital signs and physical examination findings
 
Lung injury score (LIS): The LIS is a composite 4-point scoring system including the PaO2/FiO2, positive end-expiratory pressure (PEEP), quasi-static respiratory compliance, and the extent of infiltrates determined by imaging
 
Intensive care unit-free days
 
Mean daily sequential organ failure assessment score(s) (SOFA)
 
Supportive interventions used (e.g., use of prone ventilation, paralytics, pulmonary vasodilators, and other interventions affecting oxygenation)
 
All-cause mortality rates within 30 days and at 6 months
 
 | 
 
Proportion of ventilator-free days and the corresponding 95% CI
 
Median time to extubation from dosing and the corresponding 95% CI
 
Median time to intubation from dosing in patients with mild ARDs and the corresponding 95% CI
 
Median time of intubation and the corresponding 95% CI
 
Proportion of intensive care unit-free days and the corresponding 95% CI
 
Listings of vital signs and physical examination
 
Proportion of all-cause mortality within 30 days and at 6 months and their corresponding 95% CIs
 
Plots and listings of LIS over time
 
Plots and listings of median daily SOFA score over time
 
 |

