### 4.2 General Presentation Considerations

Baseline is defined as the last available pre-treatment assessment. The end of the study is defined as the date on which the last subject completes the final follow-up visit, which may be up to 6 months after the last subject's screening date. Treatment day will be calculated relative to the date of the first treatment day such that Treatment Day = Assessment Date – First Infusion Date + 1. 6

Continuous data will be summarized in terms of the mean, standard deviation (SD), median, upper quartile, lower quartile, minimum, maximum and number of observations, unless otherwise stated. The minimum and maximum will be reported to the same number of decimal places as the raw data recorded in the database. The mean, median, lower quartile and upper quartile will be reported to one more decimal place than the raw data recorded in the database. The SD will be reported to two more decimal places than the raw data recorded in the database. In general, the maximum number of decimal places reported shall be four for any summary statistic.

Categorical data will be summarized in terms of the number of patients providing data at the relevant time point (n), frequency counts and percentages.

Percentages will be presented to one decimal place. Percentages will not be presented for zero counts.

Changes from baseline in categorical data will be summarized using shift tables where appropriate.

P-values greater than or equal to 0.001, in general, will be presented to three decimal places. P-values less than 0.001 will be presented as “<0.001”.

Wilson confidence intervals (CIs) will be presented to one more decimal place than the raw data.

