#### **4.11.1.1 Handling of Dropouts or Missing Data**

No imputation will be made for missing data resulting from an early withdrawal, missed evaluations, or any other unforeseen reason. All missing or partial data will be presented in the patient data listings as they are recorded on the eCRF.

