#### **4.11.2.1 Intubation/continuation/discontinuation of intubation/mechanical ventilation**

The time between dose and intubation, time of continuation and then time between dose and extubation can be used to measure the efficacy of the therapy.

The following parameters will be computed together with their 95% CI:

- Median time between dose and intubation
- Median time between dose and extubation
- Medium intubation continuation time

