#### **4.11.2.2 Supportive oxygenation intervention**

The length of time of oxygenation intervention is a good indication of efficacy. The median time for oxygenation intervention will be computed.

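### The SAP gives death no role in the ventilator-, ICU-, extubation- and oxygen-support outcomes, and does not state the unit of analysis for the two free-day proportions

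*Combined protocol and SAP*

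**What the plan says.** SAP Table 2 lists, among the secondary estimators, "Proportion of ventilator-free days and the corresponding 95% CI", "Proportion of intensive care unit-free days and the corresponding 95% CI", "Median time to extubation from dosing and the corresponding 95% CI" and "Median time of intubation and the corresponding 95% CI". SAP 4.11.2.1 repeats the intubation and extubation times, including "Medium intubation continuation time" (presumably median), and presents them as measures of efficacy. SAP 4.11.2.2 states: "The length of time of oxygenation intervention is a good indication of efficacy". It then plans a median with no CI.

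On intervals, SAP 4.2 says "Wilson confidence intervals (CIs) will be presented to one more decimal place than the raw data". SAP 4.11.2.4 (mortality) and 4.11.2.11 (secondary infections) name a score interval, which is the same type. No interval method is named for the medians.

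On incomplete records, SAP 4.11.1.1 says "No imputation will be made for missing data resulting from an early withdrawal, missed evaluations, or any other unforeseen reason". SAP 3.9 runs assessments to Day 32 or discharge and defines the end of hospitalization as discharge or death. No section gives a window or denominator for the free-day proportions, says whether days or patients are the unit, or says how death enters any of these outcomes. All-cause mortality within 30 days and at 6 months is a separate endpoint.

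**The concern.** Death is common in this population. In the small, selected VV-ECMO comparison of supplementary Table S1, 2 of 5 treated patients (40.0%) and 17 of 35 controls (48.6%) died. A patient who dies on Day 3 while ventilated has a short intubation and a short period on oxygen. If short support is read as activity, that patient counts in the therapy's favour.

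The free-day proportions raise two further questions. The result depends on what is done with the days after death. The width of the CI depends on whether 43 patients, or more than a thousand patient-days, count as the sample. An analyst must settle both after seeing the data. Protocol 9.2 also leaves room for a comparison with a matched control, and undefined rules would carry over into it.

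**Working it through.** The documents give no CI width, within-patient correlation or expected duration for these endpoints, so there is no planned figure to reproduce. The inputs below are assumptions unless a source is given.

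**1. Durations and extubation time.** Assume that all patients are ventilated at dosing, the extubation hazard is a = 1/18 = 0.0556 per day, the death hazard while ventilated is d = 0.005 or 0.06 per day, and follow-up runs to Day 32 (SAP 3.9). Write h = a + d, giving 0.0606 or 0.1156.

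- Deaths by Day 32, (d/h)(1 − e^(−32h)): 0.071 and 0.506.
- Median intubation time when death ends it, ln 2/h: 0.693/0.0606 = 11.4 days and 0.693/0.1156 = 6.0 days.
- Median in extubated patients only, −ln(1 − 0.5(1 − e^(−32h)))/h: 9.2 and 5.8 days.
- Kaplan-Meier median with death censored, ln 2/a: 12.5 days in both cases.
- Median of the cumulative incidence of extubation, solving (a/h)(1 − e^(−ht)) = 0.5: 13.0 days in the first case. In the second it is not reached, because a/h = 0.48.
- Cumulative incidence of extubation at Day 30: 0.77 and 0.47.

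Extubation ability is the same in both cases; only mortality differs. The first two summaries appear to improve, the third does not move, and only the cumulative incidence worsens. Oxygen-support duration follows the same logic as intubation duration.

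**2. Free-day proportions under different death rules.** With the same hazards, expected ventilated days in 32 are (1 − e^(−32h))/h = 14.1 and 8.4. Days lost after death are (d/h)(32 − ventilated days) = 1.5 and 12.2, so days alive are 30.5 and 19.8.

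| Rule | 7% deaths | 51% deaths |
|---|---|---|
| Days after death count as free: 1 − ventilated/32 | 0.56 | 0.74 |
| Pooled over days alive: (alive − ventilated)/alive | 0.54 | 0.57 |
| Death scored as 0 per patient: (a/h)(32 − ventilated)/32 | 0.51 | 0.35 |

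A mean of each patient's proportion over days alive equals the last row here, because in this model every death occurs on the ventilator and such a patient has no free days. It would differ for deaths after extubation.

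A separate simulation (N = 43, 30 days, 40% deaths, median extubation 7 days, median death at Day 5) gave 0.70, 0.57 and 0.40 under the three rules, against 0.66 with no deaths. With median death at Day 10, pooling over days alive gave 0.52, so earlier death scored better than later death. Counting days after death as free then gave 0.625, slightly below 0.66, so that rule does not always lift the result above the no-death value.

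**3. CI width if days are pooled.** With m days per patient and within-patient correlation ICC, a pooled-day interval is too narrow by the factor √(1 + (m − 1)·ICC). For m = 30:

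- ICC 0.3: √9.7 = 3.1
- ICC 0.5: √15.5 = 3.9
- ICC 0.9: √27.1 = 5.2
- ceiling, ICC 1: √30 = 5.5

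Illustration of the extreme: for p = 0.5 and 20 patients, Wilson on 20 × 30 = 600 days gives 0.460 to 0.540 (width 0.080). Wilson on 20 patients gives 0.299 to 0.701 (width 0.401). The ratio is 5.0.

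Simulation over 30 days (N = 15, 20 or 43; deaths 0 to 48.6%; median extubation 7, 14 or 28 days) gave median ratios of about 3.2 to 4.3, with 10th to 90th percentiles of single trials from 2.4 to 4.9. A second simulation (28 days, n = 43, half the patients with 0 free days, the rest uniform on 5 to 25) gave widths of 0.050 pooled and 0.189 patient-level, a ratio of 3.8, with coverage of 39% and 94%.

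**The case against.** **Pooling of days is not stated.** A reader might infer that the planned CIs are about four times too narrow. The documents do not support that as a fact. Table 2 names no unit, SAP 4.2 is a rule on decimal places, and where the SAP ties a score interval to an endpoint (mortality, secondary infections) the patient is the unit. A mean of per-patient proportions fits Table 2 as well, and its CI need not be too narrow. This stands: the factor is conditional. Nor can it extend to extubation, intubation or oxygen support, which are medians of one time per patient; oxygen support has no planned CI.

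**Death does not always look like benefit.** A reader might infer that every one of these endpoints points the wrong way. It does not. Censoring makes time to extubation blind to death, not reversed. For free days, death is under-penalised when days alive are pooled, and rewarded mainly if days after death count as free, which the SAP does not say. A per-patient average over days alive handles deaths on the ventilator correctly. What remains is that the SAP does not choose among these rules, and that the plain duration medians do reward early death.

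**The missing-data rule is weak evidence.** SAP 4.11.1.1 concerns withdrawal and missed evaluations; death is neither. It leaves the question open.

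**The endpoints are secondary and descriptive.** No hypothesis is tested, and mortality is reported separately with its own CI. A reader would see high mortality beside short durations. This lowers the severity. It does not correct a median that moves the wrong way, and SAP 4.11.2.2 still tells the reader to treat duration as efficacy.

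**Conclusion.** The concern holds in a limited form. The SAP gives death no role in five outcomes: ventilator-free days, ICU-free days, time to extubation, intubation duration and oxygen-support duration. For the two durations, taking the record as it stands rewards early death: 11.4 to 6.0 days in the illustration, under constant hazards and an assumed extubation rate. A median in extubated patients only has the same fault, and censoring at death hides the deaths. For the free-day proportions the result depends on an unstated rule (0.40, 0.57 or 0.70 in one simulated setting). If their days are pooled, the CIs would be roughly 3 to 5 times too narrow, for an ICC of 0.3 to 0.9 that the documents do not give. The change should be made before analysis. Because these are descriptive secondary endpoints with mortality shown alongside, it is not a fault that invalidates the plan.

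**What to change.** In SAP Table 2 and 4.11.2.1 to 4.11.2.2:

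1. Fix one window: Day 28, or Day 30 to match the mortality endpoint. Compute ventilator-free and ICU-free days per patient, with death in the window scored as 0. Summarise across patients with a patient-level 95% CI, for example a bootstrap over patients.
2. For patients intubated at infusion, report the cumulative incidence of extubation at the same day with death as a competing event, in place of median intubation duration.
3. For oxygen support, report the cumulative incidence of coming off support in hospital with death as a competing event, in place of median duration. Delete the sentence that its length indicates efficacy.

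Oxygen-support-free days are not proposed. Daily evaluations are recorded only during hospitalization, and after early discharge no visit is expected until the 30-day follow-up, so daily oxygen status after discharge is not collected. For the same reason, item 1 needs a written convention for days after discharge alive; re-admissions are recorded as SAEs under protocol 8.1.2 and can inform it.

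The cost is SAP wording and light programming. The CIs will be wider than pooled-day ones, and the estimates are likely to look less favourable.

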| 
 
To assess evidence of improvement and resolution of ARDS following infusion with agenT-797
 
To assess avoidance of multiorgan dysfunction syndrome
 
                                                                 | 
 
Assessment of ventilator-free days
 
Time to extubation
 
Time to intubation in patients with moderate ARDS
 
Vital signs and physical examination findings
 
Lung injury score (LIS): The LIS is a composite 4-point scoring system including the PaO2/FiO2, positive end-expiratory pressure (PEEP), quasi-static respiratory compliance, and the extent of infiltrates determined by imaging
 
Intensive care unit-free days
 
Mean daily sequential organ failure assessment score(s)
 
Supportive interventions used (e.g., use of prone ventilation, paralytics, pulmonary vasodilators, and other interventions affecting oxygenation)
 
All-cause mortality rates within 30 days and at 6 months
 
 |
| 
 
To assess evolution of cytokine release syndrome (CRS)
 
                                                                                                                                                                     | 
 
Change in clinical parameters and biomarkers relevant to CRS (D-dimers, ferritin, C-reactive protein, IL-1, and IL-6)
 
                                                                                                                                                                                                                                                                                                                                                                                                                                                                                                                                                                                                                                                                  |

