## **4.7. STUDY CRITERIA**

### **4.7.1. Patient Inclusion Criteria**

For inclusion in this trial, all the following inclusion criteria must be fulfilled. No waivers to inclusion criteria will be permitted.

1. Voluntarily agree to participate and can provide informed consent or have a duly appointed health care proxy established which/who has the authority to consent on behalf of the patient
2.  $\geq 18$  years of age
3. Inpatient hospitalization
4. Evidence of SARS-CoV-2 infection with the diagnosis of moderate to severe ARDS per Berlin definition ([ARDS 2012](#)), no more than 2 weeks prior to study enrollment
5. Patients at high risk of intubation or intubated with mechanical ventilation
6. Female patients of childbearing potential must be willing to use highly effective contraception measures starting with the Screening visit through 90 days after last dose of study treatment. Male patients with a female partner(s) of childbearing potential must agree to use highly effective contraceptive measures throughout the trial starting with the Screening visit through 90 days after the last dose of study treatment is received. Males with pregnant partners must agree to use a condom; no additional method of contraception is required for the pregnant partner

Note: Abstinence is acceptable if this is the established and preferred contraception method for the patient

7. Patients, or study participant's duly appointed health care proxy with the authority to consent on behalf of the patient, must consent to placement of a central venous access line for the administration of agenT-797

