### 3.2 Number of Patients

It is estimated that up to approximately 43 patients, requiring or at risk of needing mechanical ventilation with mild to severe ARDS, per the Berlin definition ([ARDS 2012](#)), will be enrolled into the study. Additional patients may be added at the discretion of the SMC based on the review of the totality of the data including safety and efficacy data.

No formal sample size calculations were performed since all analyses will be descriptive and exploratory of nature, without any formal testing of hypotheses.

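### SAP Table 2 estimates time to intubation in mild ARDS, which the current eligibility criteria do not admit; the protocol defines this endpoint in moderate ARDS

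*Combined protocol and SAP*

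**What the plan says.** The protocol, in Section 3 and the synopsis, lists the secondary endpoint as "Time to intubation in patients with moderate ARDS". In SAP Table 2 the same endpoint reads "Time to intubation in patients with mild ARDS", and the estimator beside it is "Median time to intubation from dosing in patients with mild ARDs and the corresponding 95% CI". The change of stratum is thus in both columns.

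On who may enter, inclusion criterion 4 (protocol 4.7.1) requires "Evidence of SARS-CoV-2 infection with the diagnosis of moderate to severe ARDS per Berlin definition", and the section opens with "No waivers to inclusion criteria will be permitted". The SAP describes the population differently: SAP 3.2 speaks of patients needing, or at risk of needing, "mechanical ventilation with mild to severe ARDS", and SAP 3.1 also says mild to severe. The corresponding protocol sections, 4.1 and 4.2, say moderate to severe.

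SAP 4.11.2.1 lists "Median time between dose and intubation" with a 95% CI. It names neither a severity stratum nor a requirement that the patient be free of intubation at dosing. SAP 4.11.2 makes the safety set the general population for clinical activity.

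**The concern.** An estimator needs patients who belong to its stated population. Here the stratum named in the SAP lies outside the eligibility criteria that govern enrolment. A programmer who follows Table 2 would expect an empty output. One who follows 4.11.2.1 would have to decide who counts as at risk, and would do so in an open-label study with the data in hand. The report could also carry the SAP's mild to severe description of a population that the protocol describes as moderate to severe.

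**Working it through.** The plan gives no sample size or precision figure for this endpoint, so there is nothing to reproduce. The check is a comparison of sets and of texts.

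**Step 1: severity strata (protocol Appendix 2, PaO2/FiO2 in mmHg).**
- Mild: above 200, up to 300
- Moderate: above 100, up to 200
- Severe: 100 or below

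**Step 2: overlap with eligibility.** Criterion 4 admits moderate or severe, that is PaO2/FiO2 of 200 or below.
- Mild and eligible: above 200 and at most 200, which is empty.
- Moderate and eligible: above 100 up to 200, which is the whole moderate stratum.

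Appendix 2 places these cut-offs under a draft definition. Its list of diagnostic requirements also asks for moderate to severe impairment of oxygenation, so that part of the appendix excludes mild disease too.

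**Step 3: does other text bring mild patients in?** SAP 3.1 and 3.2 say mild to severe, but a SAP cannot widen eligibility. Protocol 4.1 and SAP 3.1 both treat the inclusion of less severe cases as a matter for a protocol modification, and the current criteria contain none. No cohort in protocol Table 2 or SAP Table 1 is defined by mild disease. The SAP itself (3.1 and 3.4) describes Cohort 4 as moderate to severe. The planned numbers do not help either: Part 1 at 3 dose levels × 6 = 18, plus 15 in Cohort 4, gives 33. That leaves 43 − 33 = 10 patients not allocated by those two figures, and nothing links them to mild ARDS.

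**Step 4: the populations given for one endpoint.**

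| Source | Severity | Intubation status at dosing |
|---|---|---|
| Protocol Section 3 | moderate | not stated |
| SAP Table 2 | mild | not stated |
| SAP 4.11.2.1 | no restriction | not stated |

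**Step 5: who can be at risk.** Criterion 5 admits both intubated patients and those at high risk of intubation. Only the latter can have a time from dosing to first intubation. Cohort 4 is restricted to patients already on mechanical intubation, so it contributes 0 of up to 15. Any estimate must come from patients in Cohorts 1 to 3 who were not intubated at infusion. The plan does not say how many that is. The figure of 18 is not a firm ceiling, because Cohort 3 is listed as 6 or more.

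**The case against.** The strongest reply has four parts.

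*Earlier criteria.* A reader might infer that no treated patient had mild ARDS. The documents do not support that. Part 1 is marked completed, and the criteria under which it enrolled are not shown. Criteria did change by amendment: exclusion 10 applies only after Amendment 7. The SAP also names two base protocols, version 8 with Amendment 7 in its introduction and version 9 with Amendment 8 in its revision history. The mild wording may come from another version, though that is inference. This part stands, and it limits the finding to the current eligibility text.

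*Timing.* Criterion 4 allows a diagnosis up to 2 weeks before enrolment. If severity were taken at the SAP's baseline, the last assessment before treatment, a patient diagnosed as moderate could be in the mild range at dosing. This stands too, and it is a reason to state the time of classification.

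*SAP 4.11.2.1.* A reader might infer that this section sends already intubated patients into the analysis with negative times, so that the median is meaningless. It does not say so; it is an underspecified line. Post-dose intubations could still be reported under it. What is missing is an agreed population, not necessarily all information on the endpoint.

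*Weight.* This is one of nine secondary endpoints for the ARDS and organ-dysfunction objectives, in a single-arm study with a safety primary objective and descriptive analyses only. That is fair, and it sets the priority.

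None of this removes the conflict between Table 2 and the protocol. The SAP's agreement with itself on mild disease does not make those patients eligible. SAP Section 1 also requires major endpoint changes to appear jointly in a protocol amendment and a new SAP version, and the protocol supplied does not carry this one.

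**Conclusion.** Wrong as written, and should be fixed. Under the current criteria the Table 2 estimator has no eligible patients by design, whereas the protocol's moderate stratum is wholly eligible. Table 2 and 4.11.2.1 give different populations, and neither states intubation status at dosing.

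The conclusion assumes that the current inclusion criteria govern and that severity is fixed at the qualifying diagnosis. It is not a count of patients actually treated. No error rate or power is affected, and no dose or safety decision rests on this endpoint.

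A reader might also infer that the protocol's moderate group is itself wrong, and must give way to all non-intubated patients of any severity with a competing-risk analysis. The mismatch does not require that. It would redefine a protocol endpoint, and it is a matter of preference.

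**What to change.** 1. SAP Table 2: change *mild* to *moderate* in both the endpoint and the estimator column.
2. SAP 3.1 and 3.2: change *mild to severe* to *moderate to severe*.
3. SAP Table 2 and 4.11.2.1: use one analysis set, namely patients with moderate ARDS who are not intubated at the start of infusion. State the time at which severity is classified (for example at qualifying diagnosis or at the SAP's baseline), and show the number at risk by cohort.
4. Optional supplementary displays: results for all non-intubated patients regardless of severity, and death without intubation as a competing event.

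Items 1 to 3 cost SAP wording only. They need no new visit or measurement and no change to the protocol's choice of stratum.

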### **9.4. PROCEDURE FOR ACCOUNTING FOR MISSING, UNUSED, AND SPURIOUS DATA**

Missing, unused, and spurious data will be dealt with as such. There is no intention to implement any procedure for replacing missing data.

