## **4.11 Efficacy Evaluation**

### **4.11.1 Analysis and Data Conventions**

No formal testing of hypotheses has been planned in this study. All analyses will be based on descriptive statistics.

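### Time to intubation is summarised only by a median with a 95% CI, with no rule for patients never intubated or who die unintubated and no proportion intubated, so it does not reliably track avoided intubation

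*Combined protocol and SAP*

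**What the plan says.** SAP Table 2 gives the estimator as "Median time to intubation from dosing", restricted to mild ARDS and accompanied by a 95% CI. SAP 4.11.2.1 lists "Median time between dose and intubation" among the parameters to be computed with 95% CIs. It says that this time, the time on intubation and the time to extubation "can be used to measure the efficacy of the therapy".

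Neither place names Kaplan-Meier, censoring, a competing event, a time horizon or the set of patients at risk. Table 2 and SAP 4.11.2.1 to 4.11.2.14 contain no proportion or cumulative incidence of intubation.

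The general rules that could bear on the computation are:
- SAP 4.11.1: "All analyses will be based on descriptive statistics".
- SAP 4.11.1.1: "No imputation will be made for missing data resulting from an early withdrawal, missed evaluations, or any other unforeseen reason".
- Protocol 9.4: "There is no intention to implement any procedure for replacing missing data".

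Inclusion criterion 5 (protocol 4.7.1) admits patients who are not yet intubated but are likely to need it, as well as those already ventilated.

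**The concern.** For a patient not intubated at infusion, the good outcome is never to be intubated. Such a patient has no intubation time, and neither does one who dies first. A summary built only on intubation times therefore has no defined place for either the best outcome or one of the worst.

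The SAP leaves the programmer to choose. One choice takes the median over patients who were intubated, that is, over the failures. Another is a Kaplan-Meier median with unintubated patients censored. The two answer different questions and can give different results from the same data, and neither shows how many patients avoided intubation. Since the SAP presents this time as a measure of efficacy, a reader could draw a conclusion about benefit from a number that does not carry it.

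**Working it through.** **Inputs.** The documents give no intubation rate, event count or number of patients unintubated at infusion, so there is no planned figure to reproduce. Every hazard and event time below is an assumption.

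**1. Two competing outcomes.** Let *a* be the constant daily hazard of intubation and *r* that of recovery (live discharge without intubation). Over unlimited follow-up, in large samples:
- proportion intubated = a/(a + r)
- median among the intubated = ln 2/(a + r)
- Kaplan-Meier median with discharge censored = ln 2/a

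| a, r | Intubated | Median among intubated | Kaplan-Meier median |
|---|---|---|---|
| 0.10, 0.10 (reference) | 50% | 0.693/0.20 = 3.5 days | 0.693/0.10 = 6.9 days |
| 0.10, 0.20 (recovery doubled) | 33% | 0.693/0.30 = 2.3 days | 0.693/0.10 = 6.9 days |
| 0.05, 0.10 (intubation hazard halved) | 33% | 0.693/0.15 = 4.6 days | 0.693/0.05 = 13.9 days |

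The last two rows avoid the same share of intubations. The intubated-only median moves in opposite directions. The Kaplan-Meier median responds to the lower intubation hazard but not to faster recovery.

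Cutting follow-up at Day 30 multiplies the proportion by 1 − exp(−30(a + r)). This gives 49.9%, 33.3% and 33.0%, so the proportion registers the benefit in both scenarios.

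**2. A small-sample count.** Take 10 unintubated patients who, untreated, would be intubated on days 1 to 10: median 5.5 days, 10/10 intubated. Suppose 6 intubations are prevented, leaving 4/10 (Wilson 95% CI 16.8% to 68.7%). The median among the 4 intubated is then:
- 2.5 days if the 6 latest are prevented (days 1, 2, 3, 4 remain)
- 8.5 days if the 6 earliest are prevented (days 7, 8, 9, 10 remain)
- 5.5 days if the prevented ones are spread out (days 2, 4, 7, 9 remain)

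The proportion is 4/10 each time. In the 2.5-day case, if 2 of the 6 unintubated patients die on days 5 and 6, the median is still 2.5 days: the deaths leave no trace.

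**3. Death as a competing outcome.** Add a death hazard *d*, let L = a + r + d, and follow to Day 32 (the assessment horizon in SAP 3.9), with F = 1 − exp(−32L). The median among the intubated is −ln(1 − F/2)/L, and the cumulative incidence of each event is its hazard divided by L, times F.
- a = 0.10, r = 0.05, d = 0.02: median 4.05 days, intubated 58.6%, dead unintubated 11.7%, either 70.3%.
- The same with d = 0.10: median 2.77 days, intubated 40.0%, dead unintubated 40.0%, either 80.0%.

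More deaths also lower the proportion intubated, so that proportion must be read beside death. The combined outcome moves the right way.

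**4. The promised interval.** An exact order-statistic CI for a median of *n* values has coverage of at most 1 − 2(0.5)^n: 93.75% at n = 5 and 96.9% at n = 6. With 5 or fewer intubated patients, an intubated-only median has no exact 95% interval of this kind.

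**5. The population.** SAP Table 2 restricts the estimator to mild ARDS. The protocol endpoint (Section 3) is for moderate ARDS, and inclusion criterion 4 requires moderate to severe ARDS. Taken with that criterion, the SAP estimator may have no eligible patients.

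**The case against.** **The intubated-only median is an inference.** This stands. No section says so. The no-imputation rule concerns missing data, whereas not being intubated is a known outcome, and censoring is not imputation. A median with a 95% CI is equally open to a Kaplan-Meier reading. What the text establishes is that the method is unspecified and that no intubation proportion is planned.

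**A reader might infer that an effective treatment will look harmful.** The documents do not support that. The direction is not fixed: the median can shorten, stay or lengthen. Looking harmful also needs a comparison, and this is a single-arm study without tests. Protocol 9.2 says only that a matched control may be used, and the SAP defines none.

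**A reader might also infer that a Kaplan-Meier median cannot be computed once fewer than half are intubated.** That is not so with discharge censored: with 33% intubated after recovery doubles, it is 6.9 days. It does go unreached if unintubated patients are instead kept at risk to a fixed day, as in the 10-patient example (survival estimate 0.60).

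**The reach is small.** This stands. Cohort 4 enrols only intubated patients, and both documents mark Part 1 as completed, so only its unintubated patients contribute. Mortality at 30 days and 6 months, ventilator-free days and ICU-free days are reported separately, so a reader would not see this median alone. They only partly fill the gap: mortality does not show who avoided intubation, and the SAP gives no rule for deaths in ventilator-free days.

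**Conclusion.** The point holds as a gap in the estimator. Time to intubation is presented as an efficacy measure, yet its one summary is undefined for patients who recover or die unintubated, and no output counts how many were intubated. Under the assumed hazards, the same fall from 50% to 33% intubated moves an intubated-only median from 3.5 days to either 2.3 or 4.6, and a Kaplan-Meier median from 6.9 days to either 6.9 or 13.9. These figures show what can happen; they do not predict this trial. They rest on constant hazards and, for the intubated-only column, on one of two open readings.

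The change is worth making, but the effect on conclusions is limited. The endpoint is secondary and descriptive, few patients contribute, and no decision rule uses it.

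**What to change.** In SAP Table 2 and 4.11.2.1, for patients not intubated at infusion:

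1. Report the number and proportion intubated by Day 30 with a 95% score CI, as SAP 4.11.2.4 and 4.11.2.11 already do for mortality and secondary infections.
2. Show a cumulative incidence curve of intubation with two competing events: death without intubation, and live discharge without intubation.
3. Report beside it the proportion intubated or dead without intubation by Day 30.
4. Keep the median only as a description of those who were intubated, labelled as such.
5. Reconcile the endpoint population, which is mild ARDS in SAP Table 2, moderate ARDS in protocol Section 3 and moderate to severe in protocol 4.7.1. Defining the at-risk set as patients not intubated at infusion changes the stated population, so the SAP should say so openly.

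The cost is SAP wording and one table or figure. Intubation status is already an efficacy parameter in protocol 4.16.6 and mortality is already collected, so no new data are needed. The downside is precision: with so few patients the interval will be wide, as the 16.8% to 68.7% for 4 of 10 shows.
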